### Contamination reduction

When women from intervention kebeles join those women in the control kebeles during social occasions including funeral, wedding, marketing etc., there will be a possibility to contaminate the intervention messages through informal discussions of ideas regarding the intervention activities. As a result individuals from control kebeles may gain some intervention messages which may affect the intervention effect unfavorably. To reduce such an undesirable effect of information contamination, a buffer zone will be used to create non-adjacent clusters of the two study arms using clusters that will not take part in our study.

### Intervention description

The full version of the proposed intervention modality is brochure assisted home based education and counseling followed by formal invitation for cervical pre-cancer screening. The intervention will be implemented among research participants in the intervention arm. All the selected research participants who consented to participate in the intervention will be provided with the proposed intervention. Generally, the intervention will be delivered to the woman at three contact points during the intervention period. Of these contacts, the husband will take part during the second intervention schedule to receive education and counseling together with his wife. He with his wife will receive education on the key issues of cervical cancer and its screening. The husband will also be counseled on the importance and the way how he will provide support and encouragement to his wife for cervical pre-cancer screening. Finally, the woman will receive educational material during the first visit and formal letter of invitation, during the last visit, which reinforces key messages of the intervention and importance of screening for cervical pre-cancer.

The educational and counseling material is organized to address susceptibility to cervical cancer, its seriousness, the benefits of screening and barriers to screening with the objective to build cues to action and develop woman’s self-efficacy using health belief model. The intervention is organized and designed to bridge the knowledge gap and positively influence women’s belief system related to cervical cancer and its screening. This, in effect would bring positive behavior change among women to use cervical pre-cancer screening services.

The educational brochure consists of five sections. Section one provides general information on the definitions, magnitude and incidence of the disease. Section two gives information and knowledge of risk factors, signs and symptoms, complications, and preventive modalities of the disease. Section three offers an explanation of the eligibility criteria, screening schedule, benefits and barriers to screening services to encourage participants to adopt positive behaviors. Section four explains the meanings of screening results, available treatment options, cost and location of the service. Finally, section five explains the importance of male involvement in woman’s cervical pre-cancer screening uptake.

### Implementation of the intervention

Each woman will receive a total of three contacts during the intervention period. Accordingly, each eligible woman in the intervention clusters will be physically visited three times at her residential home. During the initial contact, a maximum of 45 minutes leaflet guided education & counseling session will be held with the woman to convey information on cervical cancer and its screening and counsel the woman to encourage the uptake of screening service. At the end of the session, discussion will be held with the woman to address any questions and concerns she may have. The woman will also be provided with the educational brochure for further reading at least once per week by themselves or to be read by any literate person within the family or neighborhood. The date of the subsequent follow up visit will be made consensually with the emphasis to attend the session together with her husband.

A follow up visit will be made to each woman one month after the initial visit with the objectives to re-emphasize important points of the material and make encouragement for screening. During this visit both the woman and her husband together will receive key information on cervical cancer and the importance of its screening. The husband will also be counseled on the importance and the way how the woman receives his support and encouragement to get screened for cervical cancer. Additionally any misconceptions related with the information will be corrected and barriers to screening will be addressed during this visit. Repeated follow up visits will be made in a case of absence of the couples.

Finally, the second follow up visit, which is the last visit of the proposed intervention modality, will be made one month after the first follow up visit to convey key messages about cervical cancer and its screening and address any unresolved concerns related to cervical cancer and its screening. Also, a formal letter of invitation will be granted during this visit for free screening services available in the nearby health facility. During all the visits eligible women will be asked key questions at the end of education and counseling session to check their comprehension. Also screening preparedness plan will be continuously negotiated with the woman at each visit as an encouragement for cervical cancer screening.

The intervention period lasts for six months in two phases. Phase one involves the first three months of active delivery of the proposed intervention at which time intervention will be provided to each woman in a monthly base. The second phase consists of the last three months of the intervention period. During the last three months women will not receive any intervention scheme but left unvisited with the objective to provide a period of rehearsal & translation of their knowledge in to practice. The health extension workers of the respective intervention clusters will be trained on the provision mechanisms of the intervention to couples at their homes. The overall framework of study implementation process has been depicted in the figure (Fig 1).

**Fig 1 pone.0270663.g001:**
[figure not shown]
Implementation framework of the study process.

The nature of the health problem not being widely recognized among the rural communities convinced the research team to design three home visits in the trial package. Until recent years, in a majority of the cases cervical cancer has given less attention in the health system in our country and awareness level on cervical cancer among the rural communities is generally lower than expected. As a result we planned to test the effect of structured health education and counseling approach in a home environment with three home visits.

### Standard of care

Basically families in the study clusters receive a standard of care through home visits. Generally, the usual standards of care provided to families within the health extension program through home visits are preventive and pronmotive health care services. Health extension workers provide preventive and promotive services to households at home level with the objective to develop behavioral change among households on the health care services included in the health extension packages. These services are packaged under four major program areas such as disease prevention and control; family health; personal hygiene and environmental sanitation; and health education and communication [20].

Under disease prevention and control, for example, health extension workers promote behavioral change activities that target different health problems. They also promote the utilization of health care services including disease screening services among the families. These services are common to all households within the kebele as the usual standard of care. Apart from these, the control group will not receive any innovative health care services such as structured home based couple education and counseling services during the study period. But the group will be exposed to the innovative intervention after the trial period through the routine services delivery schemes.

### Implementation of screening service

Those women who visit the screening facilities will receive the service according to the national guideline. Women will be provided with the specific information how they will access the service delivery location and whom they will contact within the health facility. Accordingly women who come from the study clusters for screening will be linked to the administrative procedures of the health facility to receive the screening service. A trained health professional will undergo assessment & counseling and conduct the screening procedure using visual inspection techniques according to the guideline. Any woman with positive precancerous screening results will receive treatment immediately after the results become available on the same day visit and be counseled to receive a follow up screening after one year. Those women who are tested negative will be counseled to receive a regular screening service after five years. All women who receive the screening will be registered on the format prepared for study purpose.

### Compliance parameter

Eligible women in the intervention clusters will be repeatedly visited in a case of absence to resolve the problem of compliance to full intervention package. Despite these efforts, due to different reasons, the eligible women in the intervention clusters may not fully comply with the proposed intervention as per the recommendations within the intervention package. This might exert undesirable effect on the uptake of the screening services. The impact of variability in the compliance to the proposed intervention requirements will be considered during analysis as a dose response function. Therefore, compliance checklist will be used to track the level of women’s compliance to our proposed intervention package to account for during data analysis.

### Trial protocol summary

We have indicated a summarized version of the intervention description in the table (Table 1).

**Table 1 pone.0270663.t001:** Summary of the intervention description.

Content of the intervention	Dosage	Frequency	Duration	Compliance parameter
Leaflet guided couple education & counseling	30–45 minutes intervention	Every month	Two months	No of couples educated & counseled
Leaflet guided couple education & counseling and formal invitation	30–45 minutes intervention	Once a month	One month	No of couples educated & counseled; and formally invited

### Primary outcome

The primary outcome of this study is the completion of cervical cancer screening test within 6 months of the baseline assessment. Participants will be interviewed using the survey questionnaire and tracked via health records review for completing the screening service. The screening proportions will be determined for each study arm at the baseline & end line. The difference in the screening proportions between intervention and control arms will be calculated. Finally, the effectiveness of the intervention will be measured as a difference of the differences in the screening uptake between the study arms.

### Secondary outcomes

We will also assess the progress of participants’ knowledge and attitude by measuring their knowledge and attitude at baseline and end line. The effect of the intervention on participants’ knowledge and attitude will be determined and compared between the study arms.

### Reliability of measures

Generally, the nature of the data collection tool we designed is adapted from different published studies and structured to fit the study context which contributes to the reliability of the measures. When we specifically come to the internal consistency of measurement items designed to measure attitude, its reliability will be assessed using Cronbach’s Alpha and appropriate corrections will be applied based on the findings of the test. The cutoff value we will use for Cronbach’s Alpha test is 0.70 or above. The other intervention we will employ to ensure the reliability of the measures will be training of the data collectors on the standards and techniques of data collection both before baseline and end line survey. Also, the same data collectors will assess study participants both during the base line and the end line survey.

### Participant timeline

The participant timeline suggesting enrolment, intervention delivery and assessment has been shown in the table (Table 2).

**Table 2 pone.0270663.t002:** Participants’ timeline of enrolment, intervention and assessment.

Activity	Month 1	Month 2	Month 3	Month 4	Month 5	Month 6	Month 7	Month 8
Participants Enrolment								
Baseline assessment								
Intervention								
End line Assessment								

### Sample size

As a requirement, we identified the proportion of current cervical cancer screening service utilization from existing literatures to be 15.5% among age eligible women [18]. This has been taken as a baseline proportion for the study and considered to be the proportion for the control arm. We will expect an absolute difference of 20% increase in screening proportions between the study arms which gives the effect size or change in screening proportion due to the intervention to be 0.2. This produces the expected end line proportions of cervical cancer screening for the study to be 35.5% and considered as the proportion for the intervention arm.

The power of the study to detect the real statistical difference is set to be 80% and 5% significance level for one-tailed test has been used. We also considered the design effect of 2 to adjust for the loss of variability that would happen due to the effect of clustering and 5% as a compensation for incomplete and non-response rates that might happen during the data collection time. Considering the above assumptions and parameters, we arrived at a total of 288 study participants basically with the help of Gpower software. The required number of clusters we determined for the study is sixteen.

### Sampling procedure

Sixteen clusters (kebeles) will be selected from the two study districts where cervical cancer screening service is currently available. Sixteen clusters are taken based on the recommendation that taking fewer subjects from many clusters give better representation of the sample than taking many participants from fewer clusters. The clusters will be randomly assigned in to intervention and control groups. Census will be carried out in the selected Kebeles to identify women who are eligible for screening and create sampling frame. Then, simple random sampling technique will be performed to select study participants from each arm. We will select equal number of participants from each cluster which consequently leads to selection of 18 participants per cluster. The same sample of participants will be used at the end of the intervention phase, six months later, to measure the outcome variables (Fig 2).

**Fig 2 pone.0270663.g002:**
[figure not shown]
Sampling procedures of the study participants.

### Data collection methods

Data will be collected using structured questionnaire designed for meeting the specific research purpose. The tool has been developed based on the research objectives from relevant literature sources. The data collection instrument will be pretested to check for its clarity, logical sequence, cultural appropriateness etc. and appropriate modification will be made accordingly. Participants will be interviewed to complete baseline survey after randomization of the clusters and end line survey at the end of the intervention period in six months. Participants will be measured for socio-demographic characteristics, knowledge, attitudes, and cervical cancer screening uptake.

Data will be collected through face to face interview technique using paper printed data collection tools contacting each woman at her residential home. Data collectors will go to each selected woman’s home physically by carrying all the data collection tools and communicate verbally with the local language to get the required information. Two different teams will be assigned for the intervention administration and data collection for the purpose of masking the intervention from data collectors. Both the baseline and end line data will be collected by the same individuals to ease the data gathering process.

### Confidentiality of the data

The information we will obtain from the participants will be kept confidential and used only for the purpose of the study. No personal identifiers will be recorded on the information and data recording sheet and only codes will be employed. The completed data checklists will be kept in a secure manner until it will be officially discarded.

### Data management

Specific cluster and individual codes will be assigned for each of the completed questionnaire. The data will be entered using Epi info version 7.2.4.0. The data will be edited and transported to either SPSS or STATA to carry out the desired statistical analysis.

### Statistical analysis

Base line screening proportions will be computed after randomization and before the intervention administration to measure the last 5 years screening performances of women in both arms with 95% confidence interval. The groups will be examined and compared at base line for any statistical differences in terms of base line participants’ characteristics and their screening experiences. The baseline characteristics will be compared using chi-square test for categorical variables and the results will be indicated in chi-square value with p-value. The continuous variables of the groups at the baseline will be compared using independent sample t-tests and the results will be shown as mean, standard deviation and p-value. A one-sided P value of 0.05 will be used to determine statistical significance.

After completing the end line survey, proportions of women that will be screened during the trial period will be calculated with the corresponding confidence interval. We will also compare the before and after intervention scores of participants’ knowledge and attitude of intervention group using paired sample t-test. A similar analysis will be done for the control group to compare the before and after intervention knowledge and attitude scores. Then we will employ the independent-sample t-test to determine the effectiveness of the intervention on knowledge and attitude by comparing participants’ knowledge and attitude scores between the two groups. The results will be computed in terms of the value of the test statistic, means, standard deviations and p-value at 5%.

Finally, we will use Generalized Estimating Equation analysis technique to test the independent effect of the intervention on the uptake of cervical pre-cancer screening services. The effect size of the intervention, confidence interval and associated P-value will be determined during the analysis. Intention to treat approach will be employed to analyze the data.

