### Randomization

The clusters or kebeles are the units of randomization in our study. Initially, eight non-adjacent clusters from each district will be identified from the two districts. Before randomization, we will stratify the clusters by the study districts and create separate list of clusters alphabetically for each district. The stratification will be done to evenly distribute any known and unknown district level confounders across the study arms. Each cluster will be assigned a unique cluster code. Then, the statistician will assign the eight clusters in to two blocks of size 4 according to the order they appeared alphabetically. The statistician will randomly select the randomization sequence of clusters for each block using the sealed lots of the six possible permutations within the block.

The clusters in each block will be randomly assigned to intervention and control arms according to the randomization sequence evident by the selected permutation within in the block for the stratum. We will repeat the same process for blocks of clusters in the other stratum. Consequently, four clusters will be obtained from each district which will form eight clusters to the intervention arm and eight clusters to the control arm maintaining 1:1 random allocation ratio. Both the stratification and randomization techniques will help actual and potential confounding factors distribute evenly across the study arms which will eventually ensure comparability of the arms.

The statistician will be made unaware of the actual study arms to mask the knowledge about which group will receive the intervention and which group will receive the usual care. This will be achieved by representing the study arms and clusters by confidential codes. Health extension workers will carry out identification of eligible participants’ for the study and subsequent intervention administration activities. Assessors will also be made blind to the nature of clusters with respect to intervention administration.

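### Baseline chi-square and t-tests ignore the randomisation by kebele and use a one-sided cut-off, so their p-values would misdescribe how comparable the arms are

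*Protocol article*

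**What the plan says.** All references are to the protocol article.

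- **Purpose** (Statistical analysis): "The groups will be examined and compared at base line for any statistical differences", covering participant characteristics and screening experience.
- **Tests** (same section): "The baseline characteristics will be compared using chi-square test for categorical variables"; "The continuous variables of the groups at the baseline will be compared using independent sample t-tests". Each is reported with a p-value, and no allowance for clustering is mentioned.
- **Cut-off**: the same paragraph ends with "A one-sided P value of 0.05 will be used to determine statistical significance".
- **Design** (Randomization): "The clusters or kebeles are the units of randomization in our study", giving "eight clusters to the intervention arm and eight clusters to the control arm maintaining 1:1 random allocation ratio".
- **Cluster size** (Sampling procedure): "selection of 18 participants per cluster".
- **Clustering allowance** (Sample size): "We also considered the design effect of 2".
- **Effect on uptake** (Statistical analysis): generalized estimating equations (GEE), under intention to treat.

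**The concern.** The plan doubles its sample because women in the same kebele resemble one another, then compares the arms at baseline with tests that assume they do not. Ordinary variation between kebeles would then be reported as a significant difference between arms more often than the nominal level implies.

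The cut-off is a second problem. The aim is to find differences of any kind, yet a one-sided t-test cannot flag imbalance in the direction it does not test, and no direction is named. A standard chi-square p-value has no direction, so a one-sided threshold is undefined for it.

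What is at stake is the account of comparability. Data collection methods places the baseline interview after the kebeles are randomised, so readers will look at the baseline table with some care. P-values that are too small, under a rule with no clear meaning, would mislead them.

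**Working it through.** **Inputs.** 8 + 8 kebeles (Randomization); 18 women per kebele, so 144 per arm (Sampling procedure); design effect 2, one-tailed 5%, power 80%, 15.5% against 35.5%, 5% allowance, total 288 (Sample size); one-sided 0.05 (Statistical analysis).

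**The plan's own figure.** The protocol states no error rate for the baseline tests, so the figure to reproduce is the sample size. The one-sided, continuity-corrected formula for two proportions gives 68 per arm. Then 68 × 2 arms × design effect 2 = 272. Adding 5% gives 272 × 1.05 = 285.6, or 272 / 0.95 = 286.3. Rounding up to 16 × 18 gives 288. The design effect of 2 is therefore built into the planned size.

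**Implied ICC.** Design effect = 1 + (18 − 1) × ICC, so a design effect of 2 means ICC = 1/17 = 0.059.

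**False-positive rate.** A test that ignores clustering uses a standard error too small by √DE. With no true difference it exceeds its critical value z in one direction with probability 1 − Φ(z/√DE). At DE = 2, √DE = 1.414:

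- One-sided 5%: 1 − Φ(1.645/1.414) = 1 − Φ(1.163) = 0.122, or 2.4 times nominal.
- Two-sided 5%, which is a standard chi-square p-value read at 0.05: 2 × [1 − Φ(1.960/1.414)] = 2 × [1 − Φ(1.386)] = 0.166, or 3.3 times nominal.
- The one-sided critical value applied in whichever direction the data fall: 2 × 0.1224 = 0.245. That is 2.4 times its own 10%, or 4.9 times 5%.

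**Simulation check.** 20,000 trials were simulated with 8 + 8 clusters of 18 and ICC 1/17. The t-test on normal data rejected 12.2% (one-sided) and 16.4% (two-sided). The chi-square on beta-binomial data, with prevalences of 0.155, 0.3 and 0.5, rejected 16.4% to 17.0% (two-sided).

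**Range.** The documents give no ICC for any baseline characteristic. The ICCs below are assumptions, with the plan's implied value included:

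| ICC | Design effect | One-sided 5% | Factor | Two-sided 5% | Factor |
|---|---|---|---|---|---|
| 0.01 | 1.17 | 6.4% | 1.3 | 7.0% | 1.4 |
| 0.02 | 1.34 | 7.8% | 1.6 | 9.0% | 1.8 |
| 0.05 | 1.85 | 11.3% | 2.3 | 15.0% | 3.0 |
| 0.059 | 2.00 | 12.2% | 2.4 | 16.6% | 3.3 |
| 0.10 | 2.70 | 15.8% | 3.2 | 23.3% | 4.7 |

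At the one-sided cut-off a factor of 3 needs a design effect of about 2.5, which is more than the plan assumes.

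**The case against.** The strongest reply is that little depends on these tests. Uptake, the primary outcome, is analysed by GEE, and the protocol makes no decision conditional on a baseline p-value. The means, standard deviations and proportions in the table are the same however the p-values are computed. All of this stands and limits the weight of the point.

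The size is also uncertain. The design effect was set for screening uptake and may not carry over to age, education or attitude. Randomisation is balanced within district, so any part of the clustering that lies between districts does not add to the difference between arms. This stands too, and is why a range is given. It does not remove the problem: in the working, the error rate exceeds nominal at every positive ICC shown.

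Some stronger readings are tempting but not supported:

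- A reader might infer roughly threefold inflation under the stated rule. At a design effect of 2 that size belongs to a two-sided 5% reading; the one-sided cut-off gives 2.4.
- A reader might infer that baseline 95% intervals would undercover to a calculable extent. The only baseline intervals named are for screening in the last five years. Participants' eligibility excludes women screened in that period, so the proportion should be zero and a normal-theory coverage figure means little.
- A reader might infer that covariates will be chosen by baseline p-value. The protocol does not say so, and naming adjustment factors can be left to the analysis plan.
- A reader might infer that the table is the trial's formal check for selective recruitment. The protocol gives it no such role.

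**Conclusion.** The point holds, with limited consequence. The tests named for baseline comparison do not respect the unit of randomisation, and the one-sided cut-off is unsuited to a balance check and undefined for a standard chi-square p-value.

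If the plan's design effect of 2 applied to a characteristic, chance rejection would be about 12.2% for a one-sided 5% t-test and 16.6% for a chi-square p-value read at 0.05. These figures rest on that assumption, on equal clusters of 18 and on a large-sample approximation that simulation supports. With a smaller ICC the inflation is modest.

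It does not follow that the effect estimate for uptake is compromised. The damage is confined to what the trial report would say about the comparability of its arms.

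**What to change.** Preferred: delete the baseline significance tests and the one-sided threshold attached to them. Describe balance by arm with individual-level summaries (counts and percentages, means and standard deviations) and cluster-level summaries across the eight kebeles per arm.

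If tests are kept, make them two-sided and cluster-adjusted. Suitable choices are GEE or a mixed model with kebele as the cluster and a small-sample correction for 16 clusters, or an analysis of the kebele summaries.

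The cost is a change of analysis wording. No additional data, participants or kebeles are needed, and the sample size is unaffected.

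### The between-arm t-test for knowledge and attitude ignores kebele randomisation; at the sample size's design effect its one-sided false-positive rate would be about 12%, not 5%

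*Protocol article*

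**What the plan says.** All references are to the Methods of the protocol article.

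- **Randomization:** "The clusters or kebeles are the units of randomization in our study". Eight kebeles go to each arm, stratified by district in blocks of four. The Sampling procedure section sets 18 women per kebele.
- **Sample size:** "We also considered the design effect of 2 to adjust for the loss of variability" due to clustering. The calculation concerns screening uptake, 15.5% against 35.5%, with "5% significance level for one-tailed test has been used".
- **Statistical analysis, scores:** before and after values are compared within each arm ("knowledge and attitude of intervention group using paired sample t-test", and likewise in the control group). The effect of the intervention is then judged between arms: "Then we will employ the independent-sample t-test to determine the effectiveness of the intervention on knowledge and attitude". The outputs listed are the test statistic, "means, standard deviations and p-value at 5" per cent. No cluster term is mentioned.
- **Statistical analysis, uptake:** GEE is named for screening uptake alone.
- **Statistical analysis, level:** "A one-sided P value of 0.05 will be used to determine statistical significance".

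**The concern.** Women in one kebele share a community and the health extension workers who deliver the intervention, so their scores are likely to be correlated. A between-arm comparison then has to be judged against the variation between kebeles. An ordinary t-test judges it against the variation between women and uses 286 degrees of freedom where the design supplies about 14.

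The plan allows for this in its sample size and names a method for correlated data for uptake, but not for the scores. Knowledge and attitude are the declared secondary outcomes and appear in the trial's objective. A chance difference between two sets of eight kebeles would be reported as an intervention effect more often than the stated level allows, in a trial whose findings are meant to inform scale-up.

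**Working it through.** **1. Reproduce the plan's sample size, to confirm how it uses one-sidedness and the design effect.** Inputs from Sample size: 15.5% and 35.5%, power 80%, one-sided 5%, design effect 2, 5% non-response. The two-proportion formula with continuity correction gives 68 per arm.
- Total: 2 × 68 = 136
- With design effect: 136 × 2 = 272
- With non-response: 272 × 1.05 = 286, or 272 / 0.95 = 287
- Rounded to equal clusters: 16 × 18 = 288, the stated figure

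The two-sided variants tried give 299 to 354. The one-sided level and the design effect of 2 are thus what the plan works with.

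**2. ICC implied by that design effect.** Design effect = 1 + (m − 1) × ICC with m = 18, so ICC = (2 − 1)/(18 − 1) = 0.059.

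**3. Standard error.** The ordinary t-test understates it by the factor 1/√2 = 0.707, so it is about 29% too small.

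**4. True error of the ordinary between-arm test.** With design effect D, the one-sided rate is 1 − Φ(1.645/√D) and the two-sided rate is 2 × [1 − Φ(1.96/√D)].

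| ICC | D = 1 + 17 × ICC | One-sided 5% test | Two-sided 5% test |
|---|---|---|---|
| 0.02 | 1.34 | 7.8% | 9.0% |
| 0.059 | 2.00 | 12.2% | 16.6% |
| 0.10 | 2.70 | 15.8% | 23.3% |

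At D = 2 these are 12.2/5 = 2.4 times nominal one-sided and 16.6/5 = 3.3 times two-sided. A simulation of 100,000 null trials (8 + 8 clusters of 18, ICC 0.059) gave 12.2% and 16.5%.

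**5. Does a cluster-level test repair it?** In the same simulation a t-test on the 16 kebele means (14 degrees of freedom) gave 4.9% one-sided and 4.9% two-sided.

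**6. Effect of the stratification.** Each district contributes four kebeles to each arm, so a district component of the ICC cancels from the arm difference. If, as an assumption, a quarter to a half of an ICC of 0.059 lay between districts, simulation puts the ordinary t-test at about 10.6% to 9% one-sided and about 13.8% to 11% two-sided.

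**The case against.** The strongest counter-argument concerns size. The design effect of 2 was chosen for a screening proportion, and the document gives no ICC for the scores. At an ICC of 0.02 the one-sided rate is about 8%, and the stratification may reduce it further. Only secondary outcomes are involved. All of this stands, which is why the figures are conditional and given as a range. It does not rescue the test, which exceeds its nominal level throughout that range. Nor is this a detail left to an unseen analysis plan: a specific method is named, and it does not fit the design.

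A reader might infer more than the document supports:

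- **That the false-positive rate more than triples.** At a design effect of 2 this needs a two-sided test. The only sidedness stated is one-sided, and the sentence on the scores gives just a 5% level. One-sided tripling needs a design effect of about 2.52 (ICC about 0.089).
- **That the paired tests are invalid tests of the intervention.** They are before-after comparisons within an arm; effectiveness is assigned to the between-arm test. Their own inflation depends on the ICC of change scores, which is not given.
- **That confidence intervals for the scores are wrong.** None is named for them; the affected output is the p-value.
- **That omitting the baseline score makes the test invalid.** The document does not say whether endline or change scores are compared, and in a randomised trial baseline adjustment is a matter of precision.

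**Conclusion.** The named between-arm test for knowledge and attitude is wrong for a trial that randomises kebeles, and its p-values will tend to be too small. The best single figure is a true error of about 12% at the plan's one-sided 5% level (about 17% if two-sided). It rests on two assumptions: that the design effect of 2 carries over from uptake to these scores, and that none of the correlation lies between districts. Across ICCs of 0.02 to 0.10 the range is about 8% to 16% one-sided and 9% to 23% two-sided. The direction of the error does not depend on the exact value; any positive correlation between women within a kebele, beyond what district explains, produces it. The conclusion does not extend to the GEE analysis of screening uptake.

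**What to change.** Replace the between-arm t-test with one cluster-aware analysis per score. Either of these would do:

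- a mixed model with a kebele random effect, or GEE by kebele, with a small-sample correction for 16 clusters; or
- a t-test on the 16 kebele means.

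Include district, because the allocation is stratified by it, and the baseline score, which is already collected on the same women. The baseline score is there for precision, not validity. State the sidedness of the test in the same sentence. Label the within-arm paired t-tests as descriptive.

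The change is one of wording. Cluster codes are already to be recorded (Data management), the planned software (SPSS or STATA) can stay, and recruitment and data collection are untouched. The price is wider uncertainty and larger p-values for these two scores, partly offset by the baseline adjustment.
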